### Planned analyses

Statistical analyses will be conducted based on an intention-to-treat (ITT) population. Participants who are recruited and treated will be considered the full analysis set (FAS), those who complete treatment and the entire follow-up protocol will be considered the per-protocol set (PPS), and those who are treated and have at least one safety evaluation will be considered the safety set (SS). Last observation carried forward (LOCF) method will be implemented to handle the missing data from withdrawn subjects, who would be included in FAS.

Comparisons of demographic information will first be conducted to measure the balance between the two groups. Then evaluation of primary and secondary outcome will conducted as below:

Primary outcomes:

The comparison of the treatment groups with regard to the primary endpoint will be performed with the data of the Full Analysis Set as well as of the Per Protocol Set. In case the two analyses will lead to different conclusions the result of the analysis of the Per Protocol Set is deciding.

Use superiority test for analysis of primary outcome. The formal test problem is as follows:

Test problem for the complete occlusion rate at 6-month follow-up:

Let πT be the rate of complete occlusion rate of treatment group at 6-month follow-up.

Let πc be the rate of complete occlusion rate of control group at 6-month follow-up.

The superiority margin δ is 0.

Test problem:

H0: πT -πc ≥ 0

H1: πT -πc < 0

α = 0.05 (2-sided)

The alternative hypothesis will not be accepted unless the lower limit of the 95% confidence interval of the difference of occlusion rate lies above the superiority margin.

Secondary outcomes:

Immediate occlusion rate will be conducted in FAS group, while other safety evaluation will be be conducted in SS group. For quantitative data, t-test (for equal variances and normal distribution) or Wilcoxon rank sum test could be applied according to the distribution of the data. The categorical variables will be compared between study arms using Chi-square tests or Fisher's exact tests (if Chi-square test is not valid). Besides, for immediate technique success rate, 95% confidence interval of each groups and difference between groups will be estimated.

The statistical analysis process will be conducted by a statistician at the Institute of Clinical Evaluation affiliated with Beijing University, and the data will be analyzed using Statistical Analysis System (SAS) software version 9.2 (SAS Institute Inc., Cary, NC, USA).

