### Primary and secondary outcomes

The primary endpoint will be the complete occlusion rate at 6-month follow-up.

Secondary endpoints will include:

1. Immediate technique success rate.

2. Overall morbidity or mortality (assessment time point: 30 days, 90 days and 1 year post-operation).

3. Ischemic stroke or intracranial bleeding (assessment time point: 30 days, 90 days and 1 year post-operation)

4. The rate of intra-stent stenosis (assessment time point: 6 months post-operation)

5. The rate of intra-stent thrombosis (assessment time point: 6 months post-operation)

6. General adverse events (assessment time point: 30 days, 90 days and 1 year post-operation).

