### Method of allocation and randomization

All recruited subjects will be randomly allocated to either the flow diverter implantation group or the control group using a web-based platform linked to a central randomization database. According to existing research, aneurysms larger than 15 mm with posterior circulation are thought to carry a higher complication rate [26,27]. Stratification will be performed for aneurysm size (≦15 mm versus >15 mm) and aneurysm location (anterior circulation versus posterior circulation).

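### The plan announces an intention-to-treat analysis, but every analysis set it defines requires treatment, and 'treated' is not defined

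*Protocol article*

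**What the plan says.** All places are in the protocol article.

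- **Principle** (Planned analyses): "Statistical analyses will be conducted based on an intention-to-treat (ITT) population".
- **Full analysis set (FAS)** (same section): "Participants who are recruited and treated will be considered the full analysis set (FAS").
- **Per-protocol set (PPS)**: "those who complete treatment and the entire follow-up protocol will be considered the per-protocol set (PPS").
- **Safety set (SS)**: "those who are treated and have at least one safety evaluation will be considered the safety set (SS").
- **Who is randomised** (Method of allocation and randomization): "All recruited subjects will be randomly allocated to either the flow diverter implantation group or the control group".
- **Primary comparison** (Planned analyses): it "will be performed with the data of the Full Analysis Set as well as of the Per Protocol Set". If the two disagree, "the result of the analysis of the Per Protocol Set is deciding".
- **Withdrawn subjects** (Planned analyses): they are placed in the FAS, with last observation carried forward (LOCF) for missing data. The Withdrawal criteria include stopping the process early on the investigator's judgement.
- **Technique success**: "Immediate technique success rate" is the first secondary endpoint. Confidence intervals are planned for it, but no analysis set is named. The FAS is named only for the immediate occlusion rate.

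**The concern.** Intention-to-treat means that all randomised patients are analysed in the arm assigned. The article uses the term but defines no such set. A patient randomised and never treated is outside the FAS, PPS and SS alike.

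Such patients are plausible here. The Procedure section requires at least three days of antiplatelet drugs beforehand, and the article does not say where randomisation falls relative to them. The Inclusion criteria accept confirmation by CTA or MRA alone, so an access or anatomy problem may first be seen at the procedural DSA. The Withdrawal criteria list voluntary withdrawal and protocol deviation.

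The operator has to know which device is to be placed. The decision not to proceed, or to classify an attempt as treatment, can therefore depend on the arm. Exclusions of that kind are not protected by randomisation and can shift the occlusion difference in either direction.

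The Withdrawal criteria also ask that raw data be kept for subjects who were enrolled and treated. Data on untreated patients may therefore not be there to repair the analysis later.

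**Working it through.** **1. Who is in which set**

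| Patient | FAS | PPS | SS |
|---|---|---|---|
| Randomised, never treated | out by definition; in if the sentence on withdrawn subjects governs | out | out |
| Assigned device attempted and failed, or procedure stopped | depends on the meaning of *treated* | depends on the meaning of completed treatment | depends on the meaning of *treated* |
| Treated with the other technique | in, unless *treated* means as assigned | unclear | in, given a safety evaluation |
| Treated as assigned, follow-up incomplete | in | out | in, given a safety evaluation |

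For a patient withdrawn before treatment, the FAS definition and the sentence on withdrawn subjects give opposite answers. LOCF does not settle it, because such a patient has no post-treatment observation to carry forward.

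**2. The plan's own sample size**

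Inputs (Sample size section): 35% against 65%, two-sided α = 0.05, power 0.80, 1:1 allocation, 20% withdrawal.

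- Without continuity correction: n = [1.960·√(2·0.5·0.5) + 0.842·√(0.35·0.65 + 0.65·0.35)]² / 0.30² ≈ 42.4, so 43 per group.
- With continuity correction: n′ = (n/4)·[1 + √(1 + 4/(n·0.30))]² ≈ 48.9, so 49 per group and 98 in total.
- Withdrawal: 49/0.80 = 61.25, so 62 per group and 124 in total.

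Both stated figures reproduce. The sample size is not at fault.

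**3. Size of the population effect**

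The article gives no untreated share, so f is an assumption, taken from 3% to 10%. The planned 65% and 35% are read as rates among treated patients. Untreated patients count as not occluded.

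- Flow-diverter arm only: rate 0.65·(1 − f), difference 0.65·(1 − f) − 0.35.
- Equal share in both arms: difference 0.30·(1 − f).
- Power at 62 per group, no continuity correction: Φ{[d·√62 − 1.960·√(2·p̄(1 − p̄))] / √(p₁(1 − p₁) + p₂(1 − p₂))}, where d is the difference, p₁ and p₂ the two rates and p̄ their mean.

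| f | Flow-diverter rate, one arm only | Difference, one arm only | Power, one arm only | Difference, both arms equal | Power, both arms equal |
|---|---|---|---|---|---|
| 0% | 65.0% | 30.0 points | 92.6% | 30.0 points | 92.6% |
| 3% | 63.1% | 28.1 | 88.7% | 29.1 | 91.0% |
| 5% | 61.8% | 26.8 | 85.5% | 28.5 | 89.8% |
| 10% | 58.5% | 23.5 | 75.2% | 27.0 | 86.5% |

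**4. If there is no true difference**

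Suppose both all-randomised rates are 35%, and a share f of the flow-diverter arm, none of them occluded, is excluded. The observed flow-diverter rate becomes 0.35/(1 − f): 36.1%, 36.8% or 38.9% for f = 3%, 5% or 10%. With 62·(1 − f) against 62 patients, the chance of a significant result favouring the device is about 3.3%, 4.0% or 6.4%, instead of 2.5%.

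**The case against.** The strongest objection is that the article does not say what the harsher reading needs.

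- **Failed devices.** A reader might infer that patients in whom the assigned device could not be used drop out of the FAS. The definition asks for treatment, not for treatment with the assigned device. A failed deployment, or a patient then given stent-assisted coiling, can be read as treated and kept. This stands: the article permits exclusion but does not prescribe it.
- **Procedures stopped early.** A reader might infer that these patients leave the FAS. Early termination is a withdrawal reason, Table 1 applies the withdrawal criteria during the procedure, and withdrawn subjects are said to be in the FAS. On that sentence they stay. This stands for anyone whose treatment has begun. It does not resolve the conflict for those withdrawn before treatment.
- **Technique success.** A reader might infer that this rate is forced towards 100% because failures are removed. No set is named for this endpoint, and the planned confidence intervals suggest that failures are expected. The earlier single-center study kept its poorly opened device in the denominator (32/33). What remains is narrower: every defined set requires treatment, so never-treated patients are missing whichever is used.
- **Size.** A loss in one arm only is the unfavourable case. Eligibility requires suitability for both techniques and excludes patients without access or with unsuitable anatomy, which limits such losses. If those without the flow diverter received stent-assisted coiling at the planned 35%, the arm's rate would be 0.65·(1 − f) + 0.35·f. The difference would then be 0.30·(1 − f), or 29.1 to 27.0 points for f = 3% to 10%. This stands as the milder end of the range.

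**Conclusion.** The contradiction is certain from the text. The plan claims intention-to-treat, but its primary comparison uses two sets that both require treatment, and *treated* is left open. The rule that the PPS decides in a disagreement moves the conclusion further from the stated principle.

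The size is not known, because it depends on an untreated share that the article does not give. For an assumed 3% to 10% in the flow-diverter arm only, counted as not occluded, the planned difference falls by about 2 to 6.5 points. For equal shares in both arms it falls by 0.9 to 3 points. At the planned effect this would seldom reverse the conclusion. It matters more if the true effect is small or the losses are lopsided. The document does not show that failed-device patients will be excluded or that technique success will be inflated; it leaves both open. This should be corrected, but it does not invalidate the design.

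**What to change.** 1. Define the FAS as all randomised patients, analysed in the arm assigned. Use *treated* for the safety set only, and define it there.
2. Name this FAS as the set for immediate technique success, and count patients without the assigned procedure as technique failures.
3. Count untreated patients without a 6-month DSA as not occluded, and say that this replaces LOCF for them.
4. Bring the sentence on withdrawn subjects into line with the new definition, and keep the data of all randomised patients.
5. Let this FAS decide the primary conclusion, with the PPS as supporting analysis. Without this step, a corrected FAS could still be overruled.

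The cost is a few sentences in the protocol and analysis plan, plus follow-up of untreated patients. Rates will be somewhat less favourable. At 62 per group with all randomised patients analysed, power falls from 92.6% to 88.7%, 85.5% or 75.2% if 3%, 5% or 10% of the flow-diverter arm alone is untreated. It stays at 86.5% or above if the shares are equal in both arms. On these figures the planned 124 patients need revisiting only if a one-sided share near 10% is thought realistic.

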#### *Withdrawal criteria*

Patients who have been included in this trial and have given written informed consent but are not able to complete the whole study for any reason will be withdrawn, including circumstances as below:

1. The subjects voluntarily quit the trial for various reasons.

2. Occurrence of serious adverse events. The subjects, main researchers, ethics committee, supervisor or CFDA terminate the research based on the consideration of ethics.

3. Early termination of the process based on the investigator’s judgment (to prevent development of severe complications, and so on).

4. Significant deviation in implementation, or the subject failed to comply with the protocol.

5. Lost of follow-up due to changes in working/living places, or fortuitous accident. When these fortuitous accidents occurs, including traffic accident, death,or bone fracture, et al., Close follow-up should be conducted to determine their relationship with the usage of Tubridge FD.

6. flawed or absence of informed consents.

When the subjects are withdrawn, the researcher would try their best to contact the subjects via telephone call, letter, clinic interview, et al., and document the reasons why they are withdrawn in detail; of which, those experienced adverse effects must be recorded in the CRF if the adverse effects were thought related to the devices used in this trial. All raw data of those enrolled and treated subjects must be kept including subjects withdrawn.

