### Sample size

The sample size calculation is based on the study of Mocco et al. [28], who reported the midterm results of 219 patients treated with Enterprise-assisted stent coiling. In their research, the 6-month complete occlusion rate was 40%; of these, 46.4% were cases of aneurisms smaller than 7 mm. Because the aneurysmal complete occlusion rate decreases with aneurysm size, we assume the 6-month complete occlusion rate to be 35% following Enterprise stent-assisted coiling for aneurysms larger than 10 mm. Furthermore, the 6-month complete occlusion rate for the Tubridge FD implantation is predicted to be 65% according to our previous results and to those of other studies using Silk or Pipeline implantation. Thus, at least 98 patients will need to be randomized in the ratio of 1:1 (49 in each group) to obtain a positive result (two-tailed test, significance level of α = 0.05, power (1 - β) = 0.80). Considering a withdrawn-patient maximum of 20%, the sample size will increase to at least 124 (62 in each group).

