### Planned patient follow-up

Arrangements will be made for all patients to be evaluated at discharge and 30 d (±7 d), 90 d (±15 d), and 1 year (±30 d) post-treatment, either by clinic or telephone contact. Postoperative DSA follow-up is required after 6 m (±30 d).

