### Safety and efficacy assessment

During the procedure and at each follow-up time point, information about the patients will be documented in detail. All data will be collected and analyzed by an independent central laboratory to compare the complication rate, morbidity, mortality, as well as initial and follow-up angiographic results between the two groups. If any adverse event has occurred, the detailed symptoms, duration, severity, possible reasons, actions taken, results and other relevant information will be reported. In addition, researchers must fill out a serious adverse event (SAE) form and notify the principal investigator, institutional review board (IRB), China Food and Drug Administration (CFDA), Clinical Research Associate (CRA), and other regulatory authorities within 24 hours.

Immediate angiographic results will be classified according to Raymond’s classification for those treated with stent-assisted coiling or FD implantation combined with coils [29]. For aneurysms treated with the Tubridge FD alone, flow modifications will be defined as disrupted inflow jet, slow flow (if the contrast circulation within the aneurysm is slowed), or reduced contrast filling (if increased contrast stagnation is observed within the aneurysm at the late venous phase of the angiographic series) [30].

The angiographic results will be classified into four categories when compared with the immediate degree of embolization: 1) Occluded, defined as no contrast filling into the aneurysm sac; 2) Improved, defined as decreased contrast filling into the aneurysm sac; 3) Stable, defined as unchanged contrast filling into the aneurysm sac; 4) Recanalized, defined as increased contrast filling into the aneurysm sac. The intra-stent stenosis will also be documented.

Table 1 shows a summary of the intervention and follow up.

**Table 1 T1:** Summary of measurement items and point of data capture

**Point of data capture**	**Pre-procedure**	**During procedure**	**Post-procedure**					
			**24 hours**	**Discharge**	**30 days**	**90 days**	**6 months**	**1 year**
Window phase					±7 d	±15 d	±30 d	±30 d
Informed consent form	√							
Inclusion/exclusion criteria	√							
Withdrawal criteria		√			√	√	√	√
Medical history/demographic information	√							
Physical examination (1)	√			√			√	
Vital signs (2)	√	√		√				
Routine urine and blood test	√			√				
Blood biochemistry test (3)	√			√				
Blood lipid test (4)	√							
Pregnancy tests (5)	√						√	
CTA, MRA or DSA	√							

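### LOCF in the full analysis set replaces a missing 6-month angiogram with the procedural image, which has no occlusion grade for Tubridge-alone patients and is likely to shrink the treatment difference

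*Protocol article*

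**What the plan says.** - **Endpoint** (Primary and secondary outcomes): "The primary endpoint will be the complete occlusion rate at 6-month follow-up".
- **Missing data** (Planned analyses): "Last observation carried forward (LOCF) method will be implemented to handle the missing data from withdrawn subjects, who would be included in FAS". The FAS consists of recruited and treated patients. It is one of two sets used for the primary comparison, in a section that takes intention-to-treat as its basis. If the FAS and the per-protocol set (PPS) lead to different conclusions, the PPS decides, and the PPS requires the whole follow-up.
- **Angiography times** (Table 1; Planned patient follow-up): DSA is ticked during the procedure and at 6 months only. The 30-day and 90-day contacts may be by telephone.
- **Grading of the immediate image** (Safety and efficacy assessment): Raymond's classification for stent-assisted coiling and for flow diverter plus coils. Otherwise: "For aneurysms treated with the Tubridge FD alone, flow modifications will be defined as disrupted inflow jet, slow flow", or reduced contrast filling. None of these levels is complete occlusion.
- **Grading at follow-up** (same section): occluded, improved, stable or recanalized, by comparison with the immediate result.
- **Planning assumptions** (Sample size): "we assume the 6-month complete occlusion rate to be 35% following Enterprise stent-assisted coiling for aneurysms larger than 10 mm"; "the 6-month complete occlusion rate for the Tubridge FD implantation is predicted to be 65"%; and "Considering a withdrawn-patient maximum of 20"%.

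**The concern.** LOCF is defensible only if the earlier value is on the same scale as the endpoint and is a reasonable stand-in for it. Neither condition is met here.

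The only angiogram before 6 months is the one taken at the procedure. For a Tubridge-alone patient it carries no occlusion grade, so someone must later decide whether to score the patient as not occluded, to regrade the image or to drop the patient. Each choice gives a different FAS result. The Background describes the device as promoting thrombus formation in the sac, so the procedural image also precedes the effect under test. For a coiled patient the image does have a grade and may be carried forward as a success, although the Discussion cites recanalization of 19.2% to 50% after reconstructive treatment such as stent-assisted coiling.

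At stake is the FAS estimate of the primary endpoint, which stands for the intention-to-treat analysis.

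**Working it through.** **1. The plan's own figure.** For 35% v 65%, two-sided 0.05 and 80% power, the standard two-proportion formula gives 43 per group without and 49 with continuity correction. The stated 49 is reproduced. 49/0.80 = 61.25, rounded up to 62 per group, 124 in total, also as stated. The sample size is not in question.

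**2. What LOCF does to the rates.** Let m be the fraction missing, unrelated to outcome (assumption). Let q be the immediate complete-occlusion rate after coiling and f the rate in the flow-diverter arm. The documents give neither.

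- Analysed control rate = (1 - m) x 0.35 + m x q
- Analysed flow-diverter rate = (1 - m) x 0.65 + m x f

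At m = 0.20 these are 0.28 + 0.2q and 0.52 + 0.2f, so the difference is 0.24 + 0.2(f - q). Two things follow:

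- The difference falls below 30 points unless f exceeds q by at least 30 points.
- The control rate rises above 35% only if q exceeds 35%.

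**3. Size.** Power is the exact binomial probability, at 62 per arm, that the lower 95% limit for the difference lies above 0. This is the article's decision rule; the Wald interval is my assumption.

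| Missing | q (coiling) | f (flow diverter) | Control v flow diverter | Difference | Power |
|---|---|---|---|---|---|
| none | - | - | 35% v 65% | 30 | 93.5% |
| 20% | 20% | 10% | 32% v 54% | 22 | 72% |
| 20% | 20% | 0% | 32% v 52% | 20 | 64% |
| 20% | 40% | 0% | 36% v 52% | 16 | 46% |
| 20% | 60% | 10% | 40% v 54% | 14 | 37% |
| 20% | 60% | 0% | 40% v 52% | 12 | 29% |
| 20% | 40% | 40% | 36% v 60% | 24 | 79% |
| 10% | 20% | 0% | 33.5% v 58.5% | 25 | 82% |
| 10% | 60% | 0% | 37.5% v 58.5% | 21 | 68% |

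The row with 40% in both arms shows what happens if the flow-diverter arm behaves at once like the coiled arm, for instance because many of its patients also receive coils. If half receive coils and 40% of those are immediately occluded, f = 0.5 x 0.40 = 20%. The comparison is then 36% v 56%, 20 points, power 64%.

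**4. One common rule instead.** Counting every missing 6-month DSA as not occluded, at 20% missing: 0.8 x 0.35 = 28% v 0.8 x 0.65 = 52%, 24 points, power 80%.

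**The case against.** **The PPS decides on disagreement.** This stands as a limit on the damage: the LOCF result cannot override the PPS, so the powers above describe the FAS analysis and not the trial's final decision. It does not repair the FAS estimate. A distorted FAS also makes disagreement more likely, which hands the conclusion to the patients who completed follow-up.

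**Part of the flow-diverter arm can be graded.** This stands too. Patients given coils as well have a Raymond grade, and the article does not give their share. The larger that share, the smaller the distortion.

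**20% is a maximum, and 93.5% is a generous benchmark.** Both are fair. At 10% missing, with nothing credited to the flow-diverter arm, power is 68-82%. With only the 49 evaluable patients per arm that the plan was sized for, the same decision rule has power of about 86%.

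**The bias runs against the device.** It does if Tubridge-alone withdrawals are scored as not occluded, and then it does not manufacture a benefit. If they were dropped as ungradable, with a coiling rate of 20%, the comparison would be 32% v 65%, or 33 points, which overstates the effect. The text does not settle which applies.

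**The analysis plan may settle it.** It may add detail, but the protocol has already named LOCF. This is a method fixed badly and not a missing detail.

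A reader might infer two stronger things. One is that LOCF must push the arms in opposite directions. That needs an immediate coiling rate above 35%, which the documents do not give. If 19.2-50% of initial occlusions reopened and none progressed, the rate would be 0.35/0.808 = 43% to 0.35/0.50 = 70%, and the analysed control rate 36.7-42.0%. Later progression to occlusion after coiling could reverse that. The other is that a coiled patient who dies will be counted as occluded at 6 months. Withdrawal criteria lists death among accidental events in the loss-to-follow-up item ("including traffic accident, death,or bone fracture") but does not say how it is scored for occlusion. The rule leaves that outcome possible without prescribing it.

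**Conclusion.** The point holds in a limited form. As written, LOCF substitutes a procedural image that does not measure 6-month occlusion in either arm and has no occlusion grade for Tubridge-alone patients. If those patients are scored as not occluded, the FAS difference is likely to shrink: to 12-22 points instead of 30, with power 29-72%, at 20% missing and under the assumed immediate rates of 20-60% and 0-10%. The loss is smaller with fewer withdrawals or with more flow-diverter patients who also receive coils. All these figures rest on missingness unrelated to outcome and on immediate rates that are assumed.

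The documents do not support saying that the control rate necessarily rises, that the trial's overall power falls to these values, or that the sample size is wrong. This should be fixed, but given the PPS rule it does not by itself undermine the trial's conclusion.

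**What to change.** - Delete LOCF for the 6-month occlusion endpoint.
- In the FAS, count death or no 6-month DSA as not completely occluded, in both arms alike. This is defined for every patient whatever the device or use of coils, and it settles how death is scored.
- Add a sensitivity analysis by multiple imputation, by arm and the two stratification factors (aneurysm size and location).

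The cost is wording in the protocol and analysis plan plus one sensitivity analysis. The downside is that both observed rates come out somewhat lower: at 20% missing, 28% v 52% instead of 35% v 65%, with power of about 80%. The proposed rule therefore also shrinks the difference, to 24 points, but by the same stated rule in both arms. No increase in sample size is needed to keep about the planned 80% under these assumptions.

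### In a superiority trial declared as intention-to-treat, the per-protocol set overrules the full analysis set on the primary endpoint, so post-randomisation exclusions can bias the deciding comparison in either direction

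*Protocol article*

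**What the plan says.** All of the following is in the protocol article.

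- Planned analyses, opening: "Statistical analyses will be conducted based on an intention-to-treat (ITT) population".
- Planned analyses, populations: the full analysis set (FAS) is limited to participants recruited and treated, and withdrawn subjects are kept in it by last observation carried forward (LOCF). For the other set, "those who complete treatment and the entire follow-up protocol will be considered the per-protocol set (PPS"). The safety set is defined separately, as those treated with at least one safety evaluation.
- Planned analyses, primary outcomes: "Use superiority test for analysis of primary outcome", and "The superiority margin δ is 0". Superiority is not accepted "unless the lower limit of the 95% confidence interval of the difference of occlusion rate lies above the superiority margin". The comparison is run in both FAS and PPS, and then: "In case the two analyses will lead to different conclusions the result of the analysis of the Per Protocol Set is deciding".
- Primary and secondary outcomes: "The primary endpoint will be the complete occlusion rate at 6-month follow-up".
- Planned patient follow-up and Table 1: DSA at 6 months, with a further contact at 1 year.
- Withdrawal criteria: reasons include voluntary exit, an item beginning "Occurrence of serious adverse events", early termination on the investigator's judgment, significant deviation or non-compliance, and loss to follow-up, with death among the listed accidents.

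**The concern.** The tie-break sentence contradicts the intention-to-treat statement that opens the same section. When the two sets agree, the PPS gives the trial's answer; when they disagree, the PPS gives it again. The FAS result can never change the conclusion.

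Membership of the PPS is settled after randomisation, by events that may depend on the device received and on how the aneurysm responded. In a superiority trial, selective exclusion can create a difference that does not exist or hide one that does. The set is also badly matched to its endpoint: occlusion is read at 6 months, yet membership requires follow-up to 1 year, so an observed primary outcome can be discarded for a missed later contact. At stake is the trial's single primary claim.

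**Working it through.** **1. The plan's own sample size.** Inputs from the Sample size section: 35% against 65%, two-sided α = 0.05, power 0.80, 1:1, 20% withdrawal.

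- Uncorrected: n = [1.96·√(2·0.5·0.5) + 0.8416·√(0.35·0.65 + 0.65·0.35)]² / 0.30² = (1.386 + 0.568)² / 0.09 = 42.4, so 43 per group.
- With continuity correction: (42.4/4)·[1 + √(1 + 4/(42.4·0.30))]² = 48.9, so 49 per group.
- 49/0.80 = 61.25, so 62 per group and 124 in total.

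The stated 98 and 124 reproduce. The point does not rest on a sample-size error.

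**2. Can the rule reverse the conclusion?** I take the success rule to be a Wald 95% interval for the difference with its lower limit above 0. (The printed H0 and H1 run the other way from this rule. That is a separate matter.) Interval: (a − b) ± 1.96·√[a(1−a)/n + b(1−b)/m]. Invented counts, with at most 12 of 62 withdrawn per arm (19%):

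| Flow diverter vs control | Set | Difference (95% CI), points | Superior? |
|---|---|---|---|
| 30/62 vs 22/62 | everyone | 12.9 (−4.3 to 30.1) | no |
| 30/50 vs 22/58 | 12 and 4 non-occluded removed | 22.1 (3.6 to 40.5) | yes |
| 35/62 vs 22/62 | everyone | 21.0 (3.8 to 38.1) | yes |
| 35/58 vs 22/50 | 4 and 12 non-occluded removed | 16.3 (−2.3 to 35.0) | no |

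In each pair the second row would decide the trial. The reversal can go in either direction.

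**3. Chance of a false superiority claim.** True rate 35% in both arms, 62 per arm. Each non-occluded patient is lost from the PPS with the probability shown; occluded patients stay. Values are by exact binomial enumeration.

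| Loss among non-occluded: flow diverter / control | False superiority |
|---|---|
| 0 / 0 | 2.6% |
| 10% / 0 | 5.0% |
| 20% / 0 | 8.9% |
| 30% / 0 | 15.4% |
| 20% / 10% | 5.2% |
| 20% / 20% | 2.8% |
| 0 / 20% | 0.65% |

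Simulation agrees to about 0.1 point. It also gives 2.6% when 20% or 30% of the flow-diverter arm is lost for reasons unrelated to occlusion and no controls are lost.

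The mechanism is the expected rate among those who remain, 0.35 / [0.35 + 0.65(1 − q)]. For q = 10%, 20% and 30% this is 37.4%, 40.2% and 43.5%. The share of the arm lost is 0.65q, that is 6.5%, 13% and 19.5%. Each is within the plan's 20% allowance, although the plan applies that allowance to both groups equally.

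**4. Power if everyone counts.** At 62 per group and 35% against 65%: z = (0.30·√62 − 1.386)/0.6745 = 1.447, power 92.6%. If 20% of each arm is withdrawn and counted as not occluded, the rates become 0.8·35% = 28% and 0.8·65% = 52%: z = (0.24·√62 − 1.358)/0.6717 = 0.792, power 78.6%.

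**The case against.** The strongest reply is that the documents do not show a bias in favour of the flow diverter. The figures of 5%, 9% and 15% come from losing only non-occluded flow-diverter patients and no controls. Equal selective loss leaves the error near nominal, loss unrelated to occlusion does nothing, and control-only loss makes the analysis conservative. That stands: 15% is an extreme scenario, not an expected effect.

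Two further inferences are tempting and also go too far.

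- A reader might infer that every patient with a complication leaves the deciding comparison. The PPS definition does not say so. A patient who has a stroke and completes treatment and follow-up stays in; only a complication that leads to withdrawal, death or incomplete follow-up removes the patient. The withdrawal item beginning "Occurrence of serious adverse events" goes on to describe termination on ethical grounds, so it does not clearly withdraw everyone with such an event.
- A reader might infer that harms disappear from view. They do not: safety outcomes are analysed in the safety set, and the tie-break governs only the occlusion endpoint.

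It is also fair to say that promoting the FAS would not by itself deliver intention-to-treat. That set is limited to treated patients and relies on LOCF. Before the 6-month DSA the only angiogram on study treatment is the procedural one, and for the Tubridge alone the immediate result is recorded as flow modification, not on Raymond's scale. This bears on the remedy and does not rescue the rule.

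An unseen analysis plan does not answer the point either. The rule is stated outright in the published text, and nothing elsewhere in the article reverses it.

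**Conclusion.** The point holds. The deciding set contradicts the declared intention-to-treat basis and is chosen by post-randomisation events, one of which, a missed 1-year contact, has no bearing on a 6-month endpoint. The rule can turn a negative full-set result positive or a positive one negative.

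The size depends on who leaves. From a nominal 2.5%, the false-superiority chance ranges from about 0.7% (20% of non-occlusions lost in control only) through about 2.8% (20% in both arms) and about 5% (20% against 10%) to about 15% (30% in the flow-diverter arm only). These results assume a true rate of 35% in both arms, 62 per arm, a Wald interval, and loss confined to non-occluded patients. The documents give no rates of loss by arm or outcome, so neither the direction nor the size of any bias is established. What is established is that the plan leaves its one primary claim open to it.

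**What to change.** In Planned analyses:

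1. Delete the sentence that makes the PPS deciding.
2. State that the primary conclusion rests on all randomised patients, analysed as allocated, and redefine the FAS accordingly.
3. For the primary endpoint, replace LOCF with a stated rule for a missing 6-month DSA, for example counted as not completely occluded, with a multiple-imputation sensitivity analysis.
4. Keep the per-protocol analysis as supportive, and require for it only the assigned treatment and a 6-month DSA, not the 1-year contact.

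The cost is a few sentences in the protocol and analysis plan. N stays at 124. Counting missing DSAs as failures costs some power: about 79% if 20% of each arm is withdrawn, against the planned 80%.
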